### 3.11. Secondary Outcomes

There will be four secondary outcomes. The first one, The Responsive Augmentative and Alternative Communication Style Scale (RAACS), will be used to measure interaction between a parent or carer, and the child at pre-intervention, post-intervention, and 2 month follow up. The second one, Paediatric Quality of Life Inventory (PedsQL), will rate the levels of difficulty in a number of areas. The third one will measure the upper limb reach. The fourth one will measure the sleep quality.

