### 3.17. Assessment Time Points (Data Collection)

Table 1 shows the study timeline and participant journey for assessment time points and data collection. Figure 2a,b are flow charts describing the processes for the baseline and intervention periods in the study and should be read in conjunction with Table 1.

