#### Outcome Evaluation

Primary and secondary outcome measures across activity and participation domains will be completed at baseline (b1–b7, with baseline length randomly allocated), during intervention (for repeated measures such as PQRS, sensor based data and accelerometers) (t1–t8), post intervention (p1, p2) and follow up (f1, f2) and include the COPM, PQRS, seat occupancy, RAACS, Peds-QL, time to target, path complexity, reaching performance and sleep quality.

Response will be tracked using multiple video recordings during sessions of goals identified for intervention as well as with sensor data and data from accelerometer. The Performance Quality Rating Scale (PQRS) will be used for goals, and sensor data for seat occupancy, and frequency and intensity of movement in bed as an indicator of sleep quality. Data points will be collected at baseline (b1–b7), during intervention (t1–t8); post-intervention (p1) and 2 month follow up (f2). There will be a minimum of 3 video-recorded baseline assessments of each goal before intervention and minimum of 3 trials post intervention and at 2 months review. Further, outcome evaluation measures outlined above will be completed at t1 and t2. The PQRS will be rated by an independent observer using video recordings. The videos from baseline, post-test and follow up will be presented in a randomized non-chronological order. A third party will complete assessments at baseline and post treatment. PQRS will be scored blinded by another occupational therapist using video recordings randomly presented.

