#### 3.19.2. Sensor Data Analysis

See Table 2 for a summary description of the data to be collected and the proposed derived parameters for further analysis.

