**ASSESSMENTS**																							
GMFCS	X																						
mini-MACS/MACS	X																						
Demographics	X																						
BFMDRS (Dystonia)	X																		X				
**TIMEPOINT**	e1	b1	b2	b3	b4	b5	b6	b7	c1	c2	t1	t2	t3	t4	t5	t6	t7	t8	p1	p2	f1	f2	cc1
PQRS (Task Performance)		xxx	xxx	xxx	xxx	xxx	xxx	xxx			xxx	xxx	xxx	xxx	xxx	xxx	xxx	xxx	X				
COPM (Goal Attainment)		X																		X		X	
Seat Occupancy (Sensor)		X	X	X	X	X	X	X			X	X	X	X	X	X	X	X		X		X	
RAACS (Communication)		X																		X		X	
Sleep Quality (Sensor)		X	X	X	X	X	X	X			X	X	X	X	X	X	X	X					
QoL (PedsQL)		X																		X		X	

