	Day Accelerations of spine (vertebra T1) and left and right thighs during seat use: ($a_{S},\;a_{TL}\;and\;a_{TR}$)	Day Intensity of motion: time averaged amplitude of xyz acceleration vector time averaged amplitude of jerk (rate of change of acceleration)	Day Motion profile—How active is the child throughout the day? Maximum and minimum motion intensities—What are the maximum and minimum activity levels? When do they occur?
9 degree of freedom motion and orientation sensor	Movement of the child’s wrist during a reaching task. Measurement of the acceleration, rotation and geomagnetic field orientation of the child’s wrist. 3 axis acceleration (accelerometers) 3 axis rotation (gyroscopes) 3 axis geomagnetic field orientation (magnetometers)	Motion path of the child’s wrist derived from acceleration and orientation data	Output parameters are to be determined from analysis of the data in the context of the video and PQRS assessment. Parameters sought are to be representative of the ‘smoothness’ and efficiency of the child’s hand motion.

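### Table 2 leaves the upper limb reach metric to be chosen from the trial data alongside video and PQRS, although section 3.17 already names reach measures and nothing says the choice is blind to phase

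*Protocol article*

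**What the plan says.** Section 3.11 of the Protocol article lists four secondary outcomes. Of reach it says: "The third one will measure the upper limb reach". It gives no metric there.

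Section 3.17 (Outcome Evaluation) ends its list of outcomes with "time to target, path complexity, reaching performance and sleep quality", so three reach-type measures are named in advance, without definitions. The same sentence gives a general schedule: "Primary and secondary outcome measures across activity and participation domains will be completed at baseline (b1–b7, with baseline length randomly allocated), during intervention", and then post-intervention and follow-up.

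Section 3.19.2 sends the reader to Table 2 for the sensor analysis: "See Table 2 for a summary description of the data to be collected and the proposed derived parameters for further analysis".

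In Table 2, the row for the 9 degree of freedom sensor fixes the body site (wrist), the task (reaching) and the intermediate product (the motion path of the wrist). It then says of the outputs: "Output parameters are to be determined from analysis of the data in the context of the video and PQRS assessment". The only limit on the choice is conceptual: "Parameters sought are to be representative of the" smoothness and efficiency of the hand's motion.

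On scheduling, section 3.17 opens with: "Table 1 shows the study timeline and participant journey for assessment time points and data collection". Table 1 has no row for reach.

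**The concern.** Each child's result is a contrast between a baseline phase in usual seating and an intervention phase in the dynamic seat. If the reach metric is settled by analysing recordings from both phases, whoever settles it may see which candidate separates the phases best. The effect estimated with that candidate will then tend to be optimistic.

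The second issue is the reference to PQRS. PQRS is a primary outcome, rated from video. A sensor measure chosen in the light of PQRS may agree with it partly because of how it was chosen. A reader who sees a wrist sensor and a blinded rating point the same way would take that as two independent lines of evidence, and the plan as worded does not secure that.

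This matters for the trial's stated purpose. Section 2.3 wants effect sizes to inform the design of future trials, and wants to know whether secondary outcomes change. An effect size from a metric selected with the phase contrast in view is a poor planning value.

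**Working it through.** The article gives no alpha, power, standard deviation or test for reach, so there is no figure to reproduce. The check sets the sections side by side.

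1. **Is reach prespecified?** Yes. Section 3.11 names it as the third of four secondary outcomes.

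2. **Are reach measures named?** Section 3.17 names 3: time to target, path complexity and reaching performance. Table 2 names 0 and says they will be determined. Section 3.19.2 describes Table 2 as containing the proposed derived parameters, which for reach it does not. It is also unclear whether reaching performance is a separate measure or a general label for the other two.

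3. **Is the gap just the brevity of an article?** The rest of Table 2 suggests not. Seat occupancy has named outputs (occupancy ratio, mean session duration, daily profile, entry frequency). Night acceleration has a sleep quality index and sleep time. Day acceleration has a motion profile and maximum and minimum intensities. Only the reach row is left open, and it states a procedure for filling the gap that depends on the data.

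4. **Is the choice protected by blinding?** Section 3.7 blinds the video raters to time of assessment, randomises the order of segments and strips dates. This protects the ratings. No section extends it to whoever chooses the reach parameters. Section 3.1 puts the child in usual seating at baseline and in the dynamic seat during intervention, so working with the video could reveal the phase even without dates.

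5. **Is reach scheduled?** Of the 4 secondary outcomes, 3 have a row in Table 1 (RAACS, PedsQL, sleep quality) and 1, reach, does not. Section 3.18, on sensor measurements, covers seat occupancy, sleep and daytime activity but not the reach sensor. The general schedule in section 3.17 covers reach, without saying which of p1, p2, f1 and f2 apply to it.

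6. **Can the reach row simply copy PQRS?** Not yet. Section 3.17 has PQRS data points at b1–b7, t1–t8, p1 and f2. The PQRS row in Table 1 ends at p1 and has no mark at f2.

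**The case against.** The strongest case on the other side has four parts.

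- **Reach is prespecified.** A reader might infer that the secondary outcome itself is selected post hoc. The article does not support that. The outcome, sensor, site, task and concept are all fixed beforehand, and three measures are named. Only the final derived parameters are open. This stands, and it limits the point to the metric.

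- **Nothing states an intention to tune the metric to PQRS.** The wording can be read innocently: video may be needed to find where a reach begins and ends in a sensor trace. This also stands. Tuning to PQRS, or inheriting its rating error, is a risk that the wording permits and not something the article plans.

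- **This is a six-child feasibility series.** Section 3.9 makes exploring the characteristics of the outcome measures one of its purposes, and the caption of Table 2 calls its analyses initial. Developing a sensor metric is legitimate work here. That answers the point only if reach is labelled exploratory or developed away from the phase contrast. As written, it is a secondary outcome.

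- **Formulas belong in the analysis plan.** Section 3.19 promises one, which is not shown. The absence of formulas from the article is therefore not a fault. The fault is that the article itself says the parameters will come from the data. An analysis plan that fixed them would still leave this text to be corrected.

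**Conclusion.** The point holds in a limited form. Table 2 makes the reach metric depend on the collected data, in the context of video and PQRS. This conflicts with the measures named in section 3.17 and with the description of Table 2 in section 3.19.2, and no safeguard against knowledge of phase is stated. Followed literally, it could bias the reach effect estimate upwards and weaken its value as corroboration of PQRS.

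No false-positive rate can be attached to this. A reader might be tempted to apply 1 − 0.95^k to k candidate metrics, but neither k nor a significance test at 0.05 for reach is in the article. The calculation also assumes independent metrics, whereas metrics from one motion path are likely to be correlated. Section 3.5 says that series size is not based on power for inferential tests of group effects, and section 3.19.1 directs its visual and Tau-U analysis mainly at PQRS.

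The missing reach row in Table 1 is a minor inconsistency, partly covered by the general schedule in section 3.17. It is not evidence of post hoc selection.

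Overall, this should be corrected before intervention data are analysed. It touches one secondary outcome and does not threaten the primary ones. The conclusion assumes that the unseen analysis plan does not already override Table 2.

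**What to change.** Reconcile sections 3.11, 3.17 and 3.19.2 with Table 2:

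- Make the reach measures already named in section 3.17 the secondary reach parameters, and enter them in Table 2. State whether reaching performance is a measure in its own right or a heading for the other two.
- If metric development is needed, do it only on baseline-phase or phase-masked recordings, and finish it before intervention data are analysed. Masking has to deal with the visible seat as well as the dates.
- Label any other reach metric exploratory.
- When reporting, do not present a metric developed with reference to PQRS as independent confirmation of PQRS.

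As a minor repair, add a reach row to Table 1 in line with section 3.17. First settle the f2 visit, where section 3.17 schedules PQRS and Table 1 shows no PQRS mark.

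The cost is wording in the text and two tables. The team gives up the freedom to choose the metric after seeing the phase contrast. It can still report further metrics as exploratory.
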